**Figure 2 F2:**
[figure not shown]
**Diagram of Park Sham device.** Reproduced from Acupuncture in Medicine, Jongbae Park, Adrian White, Clare Stevinson, Edzard Ernst, Martin James, vol 20, p 168-174, copyright 2002 with permission from BMJ Publishing Group Ltd.

Participants in the control group receive bilateral ‘needling’ on three non-acupuncture points which are not located on the same neuromuscular segments as the prescribed points used in the true acupuncture group, so as to minimise any segmental effects. Table 3 describes the sham points used. All other aspects of the sham intervention (use of the Park Sham Device base unit, needle retention time and manipulation, asking about needle sensation, treatment schedule) are as described above for the true acupuncture group.

**Table 3 T3:** Points used in the sham acupuncture group in the Acupause study (bilateral)

**Name given to point**	**Location**	**Relationship to meridians and acupoints**	**Innervation**
Abd 1	2 *cun*^a^ above and 5 *cun* lateral to the umbilicus	1 *cun* lateral to the Spleen meridian	T8/9
Arm 1	Midway between the acupoints Lung 5 and Large intestine 11 on the cubital crease		C5/6
Thigh 1	On the bulge of the rectus femoris, 5 *cun* above the middle of the superior border of the patella	2 *cun* lateral and 3 *cun* proximal to real acupoint Spleen 10	L3

^a^A *cun* is is a measurement used in locating acupoints, and corresponds to the distance between the two medial ends of the creases of the interphalangeal joints, when the patient’s middle finger is flexed.

#### Information provided to participants about acupuncture

Participants are informed, during the process for obtaining informed consent, that there is a control group, referred to as a ‘placebo’ group, and that there is a 50% chance of being randomly allocated to this group or the true acupuncture group. All participants are told that the ‘placebo’ needles are designed to stimulate different nerves compared to the true acupuncture needles, and all participants are aware that ‘placebo’ treatment is not considered active treatment. If they specifically enquire, they are told that the acupuncturists remain blinded and receive a pre-specified pack of needles and instructions as to where to insert needles for each participant after randomisation.

### Withdrawal criteria

Participants can withdraw from the trial at any time. The data collected up to the time of withdrawal will be included in the analysis unless participants specifically request for their data to be withdrawn, in which case any unprocessed data will be withdrawn from analysis. This has been made explicit in the Plain Language Statement and Consent Form. Should a participant withdraw, a detailed reason (if provided) is recorded in the trial database.

### Co-interventions

In order to avoid confounding the results of the trial, participants are asked to avoid commencing new pharmaceutical co-interventions for hot flushes during the intervention period, such as herbal treatments and HRT. If already on treatment for hot flushes, participants are requested not to discontinue this treatment during the trial.

### Outcomes

Table 4 summarises the measures and the timing of their collection during the trial.

**Table 4 T4:** Summary of measures collected as part of the Acupause study

		**Run-in**	**Intervention**			**Follow-up**	
**Measure**	**Data collection instrument**	**Baseline**	**First treatment**^ **b** ^	**4 weeks**	**8 weeks/EOT**^ **c** ^	**3 months**	**6 months**
Demographic information, risk factor for VMS	Demographics Questionnaire	✓					
VMS frequency, severity and score	Seven-day day flush diary	✓		✓	✓^a^	✓	✓
Health-related Quality of life	Menopause-Specific Quality of life Questionnaire/MENQOL	✓		✓	✓	✓	✓
Depression and anxiety measures	Hospital Anxiety and Depression Scale/HADS	✓		✓	✓	✓	✓
Credibility and expectancy	Credibility Expectancy Questionnaire + additional question on binding		✓				

^a^Primary Outcome Measure. VMS, vasomotor symptoms.

^b^Immediately after the first treatment; ^c^End-of-treatment.

#### Primary outcome measure

The primary outcome measure is the hot flush score at end-of-treatment (EOT). EOT hot flush score is calculated from the seven-day HFD which participants commence immediately upon completing their final treatment. These diaries have been used in multiple trials of interventions, and have been shown to be a consistent and reliable method of evaluating change in VMS [51].

Participants note daily in the diary the number and severity (mild, moderate, severe and very severe) of hot flushes experienced over a twenty-four hour period for seven days. The pilot study showed that it was feasible and acceptable for women to complete the diary over seven days with minimal missing data. The HFD will be used to determine three specific measurements: 1) hot flush frequency; 2) hot flush severity; and 3) a hot flush score comprising both frequency and severity. These scores are calculated as follows:

Hot flush frequency = total number of hot flushes reported/Number of days reported

Hot flush severity = (1 × number of mild hot flushes + 2 × number of moderate hot flushes + 3 × number of severe hot flushes + 4 × number of very severe hot flushes)/Number of hot flushes reported

Hot flush score = (1 × number of mild hot flushes + 2 × number of moderate hot flushes + 3 × number of severe hot flushes + 4 × number of very severe hot flushes)/Number of days reported

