### Aims and hypotheses

Our primary aim is to assess the efficacy of needle acupuncture in improving hot flush severity and frequency in menopausal women. Our hypothesis is that needle acupuncture will result in greater improvement in the severity and frequency of hot flushes compared to non-insertive sham acupuncture after ten treatments given over an eight-week period.

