### Statistical methods

Descriptive statistics will be used to summarise baseline measures and participant characteristics between the two trial groups and to assess for chance imbalance of important prognostic factors. Primary outcome is the hot flush score at EOT. Analysis will account for repeated outcome measures taken on the same women over 12 months and stratification by project acupuncturists. Mixed-effects linear regression model will be used to compare the continuous outcomes between the trial groups and marginal logistic regression model using generalised estimating equations with robust standard errors will be used for the binary outcomes. Where appropriate the baseline measure of the outcome will be included as a covariate in the regression model. In addition, factors strongly associated with the outcome and are found to be imbalanced between the trial groups at baseline will also be adjusted in the regression models. Estimates of the intervention effect will be reported as the difference in means between trial groups for continuous outcomes and odds ratios for binary outcomes, with respective 95% confidence intervals and *P*-values. Stata 13.0 [70] will be used for the data analyses.

An intention-to-treat analysis strategy will be employed where all participants will be analysed in the trial group in to which they were allocated [71]. In the first instance, we will strive to minimise the extent of missing outcome data for participants, where all efforts will be made to collect the primary outcome on participants who withdraw, discontinue their treatment or do not respond to the online survey. However, in the presence of incomplete data, information collected on the reasons for missing data will be used to inform the appropriate statistical analysis approach to handle the missing data. Sensitivity analyses that capture departures from the assumption of the missing data mechanism for the primary analysis will also be considered to assess the robustness of the results.

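### Hot flush severity is undefined for a woman with a flush-free diary, so as written it compares only women still flushing and should be descriptive

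*Protocol article*

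**What the plan says.** All references are to the Protocol article.

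- **Diary (Primary outcome measure).** Women record "the number and severity (mild, moderate, severe and very severe) of hot flushes experienced over a twenty-four hour period for seven days". The grades carry weights 1 to 4, and there is no grade of 0.
- **Frequency.** "Hot flush frequency = total number of hot flushes reported/Number of days reported".
- **Score.** The weighted sum of flushes, ending in "4 × number of very severe hot flushes)/Number of days reported". The score at end of treatment (EOT) is the primary outcome.
- **Severity.** The same weighted sum, but ending in "4 × number of very severe hot flushes)/Number of hot flushes reported".
- **Aims and hypotheses.** The hypothesis is that "needle acupuncture will result in greater improvement in the severity and frequency of hot flushes compared to non-insertive sham acupuncture".
- **Outcomes, Table 4.** The diary row reads "VMS frequency, severity and score". It is collected at baseline, 4 weeks, EOT, 3 months and 6 months.
- **Secondary outcome measures.** The score at other time points is listed. Stand-alone severity is not.
- **Statistical methods.** "Mixed-effects linear regression model will be used to compare the continuous outcomes between the trial groups". Participants are analysed as allocated. The missing-data text speaks of withdrawal, discontinued treatment and survey non-response. It does not mention a returned diary from which a measure cannot be calculated.

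**The concern.** Two of the three diary measures are averages over days, and every returned diary gives a value. Severity is an average over flushes, and a diary with no flushes gives none. Entry requires a mean score of at least 14, so every woman has a severity value at baseline. The undefined value can arise only after randomisation, and only through response.

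This matters because the hypothesis names severity as a between-group comparison. If acupuncture works, more women in the true arm should become flush-free, so that arm loses more severity values. The remaining women are no longer the groups formed by randomisation. A difference in their mean severity mixes any effect on how bad flushes are with the effect on who still has them. A null or a positive severity result would both be hard to interpret.

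**Working it through.** **1. The plan's own figure.** The sample size is stated for the score only. With difference 4, SD 11.6, two-sided 5% and 80% power, the normal approximation gives

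n per group = 2 × (1.960 + 0.842)² × 11.6² / 4² ≈ 2 × 7.849 × 134.56 / 16 ≈ 132.02, rounded up to 133.

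The exact t-test solution is 132.99, also 133. The total is 266, and 266 / (1 − 0.26) = 359.5, or 360. The stated figures reproduce. Severity does not enter them.

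**2. The three formulas for a complete seven-day diary with no flushes.**

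| Measure | Calculation | Value |
|---|---|---|
| Frequency | 0 / 7 | 0 |
| Score | (1×0 + 2×0 + 3×0 + 4×0) / 7 | 0 |
| Severity | (1×0 + 2×0 + 3×0 + 4×0) / 0 | undefined |

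**3. Are flush-free women plausible?** The plan assumes EOT mean scores of 3 (true) and 7 (sham) with SD 11.6, on a score that cannot fall below 0. As a rough check, assume mean severity 2 and negative binomial weekly counts. The weekly means are then 3/2 × 7 = 10.5 and 7/2 × 7 = 24.5. With score SD s, the weekly count SD is 7s/2, k = μ² / ((7s/2)² − μ), and P(0) = (k / (k + μ))^k.

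| Assumed score SD | True, P(0) | Sham, P(0) |
|---|---|---|
| equal to the arm's mean (3 and 7) | 7% | 4% |
| 4 | 18% | 0.1% |
| 8 | 54% | 6.5% |
| 11.6 | 71% | 21% |

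For example, at SD 11.6 in the true arm: (7 × 11.6 / 2)² = 1648.4, k = 110.25 / (1648.4 − 10.5) = 0.0673, and P(0) = (0.0673 / 10.567)^0.0673 = 0.71.

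The level depends almost wholly on the assumed SD and distribution, so none of these values is an estimate for this trial. The only stable feature is that the share is larger in the arm with the lower mean.

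**4. What the gap does to the comparison.** Take 133 evaluable women per group, assumed flush-free shares, and an assumed mean severity of 2.0 among women still flushing in both groups.

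| Flush-free, sham / true | With a severity value, sham / true | Difference, women still flushing | Difference, flush-free coded 0 |
|---|---|---|---|
| 2% / 10% | 130 / 120 | 0 | 2.0 × (0.90 − 0.98) = −0.16 |
| 5% / 15% | 126 / 113 | 0 | 2.0 × (0.85 − 0.95) = −0.20 |
| 5% / 25% | 126 / 100 | 0 | 2.0 × (0.75 − 0.95) = −0.40 |

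The last column is only the difference in flush-free share times 2.0. It is a frequency effect expressed in severity units.

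**5. The mixed model.** A flush-free woman lacks severity at that visit, not necessarily at all visits. Under missing at random, the model in effect fills the gap from her other visits and her arm. It thereby estimates a severity for flushes that did not occur.

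**The case against.** The strongest reply is that little hangs on this measure. The primary outcome is the score, which the article describes as combining frequency and severity, and a flush-free woman counts in it fully as 0. The aim can be read as carried by that score, and stand-alone severity is not listed as a secondary outcome. A convention for a zero denominator in a derived variable is also something an analysis plan would normally settle. All of this limits the weight of the point. It does not remove it: the article fixes an explicit formula, names severity in the hypothesis, and provides for missing data only of other kinds.

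Some stronger readings are tempting, and the documents do not support them.

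- **The formula hides a treatment benefit, or could show harm.** If flushes are equally severe in both arms, a difference of about 0 is the right answer for severity per flush. The apparent benefit under zero coding is the frequency effect, which score and frequency already capture. Nothing in the documents says whether women with milder or more severe flushes become flush-free, so no direction follows.
- **The best responders leave the analysis, which is then not intention-to-treat.** No text excludes them. They lack one visit's value on one non-primary measure.
- **Most of the true arm would be flush-free.** The 71% against 21% follows only if the planning SD of 11.6 is forced onto a mean of 3 under a negative binomial distribution.

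**Conclusion.** The point holds for the severity measure only. A completed flush-free diary gives 0/0, which is certain from the formula. It follows that the stated severity comparison, applied as written, is among women still flushing at each visit and is not a randomised comparison of all women.

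That the loss is greater in the better arm is probable, not certain. It rests on the trial's own hypothesis and on a score bounded at 0. The size and direction of any bias cannot be computed from the documents, and the shares and differences shown are illustrations under stated assumptions. The primary analysis, the frequency and the sample size of 266 and 360 stand. An analysis plan not shown here may already contain a rule. If so, it should be checked against the fix below.

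**What to change.** Before the group codes are revealed, add to the outcome definition that:

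- severity is calculated only for diaries with at least one flush, is conditional on still flushing, and is descriptive;
- the number and proportion of flush-free women are reported by arm beside it at each time point;
- efficacy conclusions rest on the score and the frequency, which are defined for every returned diary.

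An analysis with severity set to 0 for flush-free diaries may be added as a labelled sensitivity analysis. It should not be the main rule, because 0 lies outside the 1 to 4 scale and brings the frequency effect into severity.

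The change takes a few lines and one extra table row per time point, and needs no new data. The downside is small: the trial makes no stand-alone confirmatory claim on severity, so the severity part of the hypothesis is answered through the score.

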#### Secondary outcome measures

i. Hot flush score at other time-points: the primary outcome measure is the hot flush score at the EOT; however, hot flush score will also be measured at four weeks to assess the intermediate effect of acupuncture and at three and six months to measure longer-term outcomes as recommended in the two recent systematic reviews [27,28].

ii. Health related quality of life: the *Menopause-Specific Quality of Life Questionnaire (MENQOL)* is a validated measure of quality of life and clinical change during the menopausal transition and is specific to women in the first eight years post menopause [59]. It consists of 29 items assessing four domains: VMS, physical symptoms, psychological symptoms, and urogenital/sexual symptoms.

iii. Anxiety and Depression: *Hospital Anxiety and Depression Scale (HADS)* is a validated widely-used 14-item self-report scale designed to briefly measure current anxiety and depressive symptoms in non-psychiatric hospital patients. It excludes somatic symptoms, therefore avoiding potential confounding factors [60]. The HADS comprises two independent seven-item subscales for anxiety and depression. Anxiety has been demonstrated to be a predictor of a high placebo response in menopause studies [61].

iv. Expectancy and beliefs about acupuncture: the *Credibility/Expectancy Questionnaire* is a validated, quick and easy-to-administer six-item scale for measuring treatment expectancy and rationale credibility for use in clinical outcome studies [62]. This questionnaire is administered once, immediately after the first treatment.

v. Success of blinding: as surveys to measure the success of blinding may enhance participants’ focus on this, we measure this aspect immediately after the first treatment [63]. There is currently no validated measure to assess blinding in acupuncture research. We will use the scale developed by Bang [64], which ranges from −1 (completely not blinded) to +1 (perfectly blinded).

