### Sample size calculation

Sample size calculations are based on a two-sample *t*-test with 80% power and significance level at 5% for a two-sided test. We assumed conservatively that the mean hot flush score at baseline would be 14, the lowest possible entry score for the trial. Assuming a 50% relative reduction in the HF scores in the control group due to the placebo effect, which is the typical response reported in hot flush randomised controlled trials [69], we anticipate that women in the sham acupuncture group will have a mean hot flush score of 7 at EOT. To be clinically significant, we expect that women in the true intervention group to show at least 75% reduction in the total HF score from baseline, with a mean HF score of 3 at EOT. Based on these assumptions, 266 women (133 per trial group) will be needed to detect hot flush score difference of 4 (standard deviation (SD) = 11.6 [51]) between the two trial groups at EOT. This sample size is sufficient to detect a difference of 0.35 of 1 SD between the trial groups for the quality of life measures. Sample size was inflated to 360 women (180 per study group) to allow for attrition of 26% (experienced in the pilot study) at the measurement of the primary outcome at the EOT.

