### Blinding

The research assistant responsible for randomisation (KN) and the project acupuncturists who deliver the treatment to the women are not blind to treatment allocation. Blinding of project acupuncturists is not possible because of the difference between real and sham acupuncture points used and the tactile difference between real and sham needling.

Participants and all other investigators are blinded, including the study statistician. As outcomes are self-assessed, outcome assessment is blinded. Data analysis will be performed where the treatment groups will be identified as Group A and B. The codes for the treatment groups will be revealed after the all outcome data collection is completed at six months.

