#### Secondary analyses

Additional secondary analyses are planned. These will include (1) exploring the effect acupuncture had on women’s quality of life, (2) identifying factors that are associated with a placebo response, (such as anxiety/depression levels and demographic characteristics such as socioeconomic status), (3) the association between expectancy and beliefs and women’s response to acupuncture treatment, and (4) the credibility of the Park Sham Device.

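### The end-points of Bang's blinding index are mislabelled: +1 is complete unblinding, not perfect blinding, and 0 (chance guessing) is given no meaning

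*Protocol article*

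**What the plan says.** In the protocol article, *Secondary outcome measures*, item v (success of blinding) names a single method: "We will use the scale developed by Bang [64"]. It describes this as a scale "which ranges from −1 (completely not blinded) to +1 (perfectly blinded"). No meaning is given to 0.

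Blinding is assessed once: "we measure this aspect immediately after the first treatment [63"]. Table 4 lists the item as one extra question alongside the Credibility Expectancy Questionnaire, without its wording or response options.

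No other section prints a formula, describes reverse coding or restates the anchors. The *Blinding* section rests blinded outcome assessment on the participants: "As outcomes are self-assessed, outcome assessment is blinded".

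**The concern.** Bang's index is a named method with a fixed definition, and the labels attached to it do not fit that definition. The label for success sits on the value that shows complete failure. The value that shows guessing at chance has no label at all.

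Participant blinding carries weight here. The primary outcome is a self-completed diary, the acupuncturists know the allocation, and the two arms are needled at different points (six unilateral against three bilateral). Women whose last acupuncture was more than two years ago have been eligible since October 2011. Correct guesses, and hence positive index values, are therefore possible, and positive values are where the stated labels mislead most. Anyone applying the published labels to such a value would draw the wrong conclusion about whether blinding held.

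**Working it through.** **Inputs.** The method and its labels come from item v of *Secondary outcome measures*. The 180 women per arm come from *Sample size calculation* and serve only as illustration, since the anchors do not depend on n. The formula is the standard definition of the named method; the document does not print it. Response options of true, sham or don't know are assumed.

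**Formula, per arm.** With c correct, w incorrect and d don't know, n = c + w + d:

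BI = [2c/(c + w) − 1] × (c + w)/n = (c − w)/n, and BI = 0 if all answer don't know.

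**The plan's own figures.** The largest value is (n − 0)/n = +1 and the smallest is (0 − n)/n = −1, so the stated range reproduces. The labels do not:

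| Guesses in one arm (correct / incorrect / don't know) | BI | Meaning by definition | Reading under the plan's labels |
|---|---|---|---|
| 100 / 0 / 0% | +1 | every woman names her own arm | perfect blinding |
| 80 / 20 / 0% | +0.6 | mostly correct | towards perfect blinding |
| 60 / 20 / 20% | +0.4 | more correct than incorrect | towards perfect blinding |
| 50 / 50 / 0% | 0 | guessing at chance | midway |
| 40 / 40 / 20% | 0 | guessing at chance | midway |
| 0 / 0 / 100% | 0 | no guesses | midway |
| 0 / 100 / 0% | −1 | every woman names the other arm | no blinding |

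**Would swapping the labels, or reversing the sign, repair it?** No. If the index were incorrect minus correct, −1 would indeed be complete unblinding, but +1 would then be all-opposite guesses. Chance guessing stays at 0 under either sign, so the value for success cannot lie at an end of the scale.

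**Why the arms must be read together.** Let p be the proportion in an arm who believe they had true acupuncture, with no don't-know answers. Then BI(true) = 2p(true) − 1 and BI(sham) = 1 − 2p(sham), so their sum is 2 × [p(true) − p(sham)].

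- *Same belief in both arms.* 135 of 180 in each arm believe they had true acupuncture. BI(true) = (135 − 45)/180 = +0.5; BI(sham) = (45 − 135)/180 = −0.5; the sum is 0. Guesses carry no information about allocation.
- *Different belief.* 135 of 180 in each arm name their own arm. BI(true) = +0.5; BI(sham) = +0.5; the sum is +1.0, since belief in true acupuncture is 75% against 25%.

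The true-arm value is +0.5 in both cases, so that arm alone cannot tell them apart.

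**Why a per-arm interval is not the test.** In the first case SE = √[(1 − 0.5²)/180] = √(0.75/180) = 0.065. The 95% intervals are 0.5 ± 1.96 × 0.065, about 0.37 to 0.63, and about −0.63 to −0.37 for sham. Neither covers 0, although belief is identical in the two arms.

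**The case against.** The strongest reply is that the sentence only glosses a secondary measure. It carries no threshold, test or decision rule, and the index does not enter the primary outcome, the sample size or the regression models. The data collected are unaffected. An analyst who follows the cited source for the index, not the gloss, will interpret it correctly. All of this stands and limits the point to a correction of wording and interpretation.

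Three stronger readings are tempting, and the document does not support them.

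- A reader might infer that an unblinded arm *will* be reported as blinded. The protocol does not show whether the analysts will follow the gloss or the method's definition, so only *could* is justified.
- A reader might infer that the planned analysis of "the credibility of the Park Sham Device" is reversed. That item in *Secondary analyses* does not mention the index and may refer to the Credibility/Expectancy Questionnaire, which does not depend on these labels. The abstract lists sham credibility separately from expectancy, so the link is possible but not established.
- A reader might take +0.5 in one arm as clear proof of unblinding. In the true arm it also arises when most women in both arms believe they had true acupuncture.

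It is also fair to say that the response options are not given. A different response format could alter the scoring of individual answers. It would not make +1 perfect blinding for the index as standardly defined.

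**Conclusion.** The point holds as an error of statement. Both end-labels are wrong for the method named, and the central value is missing. At the extreme the misreading is total: all guesses correct gives +1, labelled as perfect blinding. In intermediate cases such as 60/20/20% (+0.4) or 80/20% (+0.6), a majority of correct guesses reads as leaning to success. In the sham arm, a majority believing they had true acupuncture gives a negative value, which the stated labels read as leaning to failed blinding.

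The reach is limited to the interpretation of a secondary measure that supports the participant-blinding claim. The conclusion rests on the standard definition of Bang's index and on response options of true, sham or don't know. If the analysis applies the usual interpretation, only the wording is wrong.

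**What to change.** Replace the description of the scale in item v with the three anchors, for example: *Bang's index will be calculated in each arm; +1 means all guesses are correct (unblinded), 0 means guessing at chance, and −1 means all guesses name the opposite arm.*

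Add that the two arms will be interpreted jointly. A positive true-arm value with a matching negative sham-arm value means that most women in both arms believed they had true acupuncture. Intervals may be reported, but whether one arm's interval covers 0 should not be the test of blinding.

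The cost is one or two sentences. No new data, change to data collection or change to the primary analysis is needed.
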